## ACUDIN acupuncture protocol

A total of 20 acupuncture points have been selected for the ACUDIN trial. All treatment sessions of needle and laser acupuncture are performed using the following point combination:

The 4 Bafeng points on both feet (Ex-LE-10) [47]. Needles are inserted to a depth of 3 to 5 mm and left in place without stimulation for 20 min. Laser needles are fixed with perforated plaster.

The 5 Qiduan points on both feet (Ex-LE-12) [47]. Needles are inserted to a depth of 1,5 to 2 mm and left in place without stimulation for 20 min. Laser needles are fixed with perforated plaster (Fig. 2).

**Fig. 2 Fig2:**
[figure not shown]
Illustrates the ACUDIN acupuncture point selection

The point Lianqiu on both legs (ST-34) [47]. Needles are inserted to a depth of 0,5 to 2.5 cm (depending on the diameter of the thigh) and left in place without stimulation for 20 min. Laser needles are fixed with perforated plaster.

Sterile single-use stainless steel needles size 0,2 × 15 mm are used for Qiduan and Bafeng points, respectively 0,3 × 30 mm for Lianqiu, both manufactured by Wujiang City Cloud & Dragon Medical Devise Co. Ltd, China.

### Laser acupuncture device

Laser acupuncture is performed with Laserneedle® device (European patent PCT/DE 102006008774.7), a multichannel class 3B system which allows the simultaneous stimulation of individual point combinations through semiconductor laser diodes. Flexible optical light fibers conduct the laser light without loss, providing a high optical density at the distal end [40]. Wavelengths of 685 nm (red light) are emitted in continuous mode. Each channel has an optical power of 35 mW. Power density is 2.3 kJ/cm^2^ per channel. The beam diameter is 500 μm and beam divergence at the end of the laser needle is 9.5. Laser needles are placed at an angle of 90° directly on the skin, thus radiation reflection is minimized [43]. Laser needles are plugged in silicon adapters which are fixed with perforated plaster to the skin, so they stay in place without requiring the practitioner to stay with the patient. Temperature monitoring is not required because of extremely low heat development due to the weak absorption coefficient at 685 nm [48]. Previous investigations revealed no unintended side-effects of Laserneedle® treatment [40, 48]. The use of laser protection glasses is obligatory for both study nurse and patient. Two Laserneedle® machines with 10 laser needles each are used for the ACUDIN trial.

## Procedures

### Verum needle acupuncture

The treatment is applied according to the protocol with the patient in the supine position. The practitioner inserts the acupuncture needles after local disinfection of the skin. Needles are left in place for 20 min. They are carefully removed and disposed into a bedside sharps container at the completion of treatment by study nurse 2.

### Verum laser acupuncture

The treatment is applied according to the protocol with the patient in supine position. The practitioner fixes the laser needles with perforated plaster after local disinfection of the skin. The patient’s legs and feet are covered and he/she wears laser protection glasses. The practitioner then leaves the room. Study nurse 1 enters the room and activates the laser emission by pressing at the soundless touch screen of the laser device according to the randomization schedule. Laser emission stops automatically after 20 min. Laser needles are removed and cleaned after use by study nurse 2.

### Placebo laser acupuncture

Placebo laser acupuncture is performed as described for verum laser acupuncture with slight modifications. Study nurse 1 provides the same steps as for the verum treatment but without activating the laser, pressing an invalid point at the soundless touch screen of the laser device. Therefore, from the patient’s perspective, the procedure is identical to that used in the verum laser group.

### Nerve conduction studies

The ACUDIN trial outcome measures are based on NCS parameters that are both objective and reproducible. These measures also provide quantitative data according to the Guideline for Diabetic Neuropathy [49, 50]. NCS are performed on both legs with a Neuropack-Sigma, MEB-9400, EMG/NCV/EP-System (Nihon-Khoden, Japan). Sural SNAP and tibial MNAP are measured on the first negative peak. All studies on NCS are done at room temperature (23 ± 1 °C). Sural NCS are done with standard orthodromic needle recording methods [51]. Tibial NCS are done with standard orthodromic surface electrode recording methods [51]. Skin temperatures are measured, and values of NCV are adjusted for the effect of temperature.

### Clinical examination

Clinical examinations include sensory qualities such as the perception of pain and temperature, pallesthesia and two-point discrimination, patellar and Achilles reflexes, and gait qualities. The neuropathy deficit score (NDS) [52] and the neuropathy symptom score (NSS) [52] are part of the clinical assessment. Both are validated instruments for diagnosis and progress of DPN according to the Guideline for Diabetic Neuropathy [49].

### Questionnaires to collect participants’ opinions

Common DPN-related symptoms will be recorded weekly by questionnaires using 11-point numeric rating scales (NRS) with the terminal descriptors “no complaint” and “worst complaint possible”. Whilst NRS are well validated for painful conditions [53], our questionnaires assess not only neuropathic pain but also tingling, burning pain, feeling of heat, feeling of cold, cramps, numbness, gait impairment, impairment of daily activities, sleep disturbances, and complaint frequency.

Table 1 summarizes the plan of data collection.

**Table 1 Tab1:** Baseline and outcome parameters

	Baseline parameter	Blood parameter	Neurological assessment	NCS^f^ Parameter	Subjective Score
Week 0	Age Gender Weight Size Comorbidity Medication Duration of disease (Diabetes and DPN)	HbA_1c_^a^	Clinical examination NSS NDS^c^	Bilateral amplitudes and NCV^b^of nn. surales and tibiales	NRS^d^
Week 6			Clinical examination NSS^e^ NDS	Bilateral amplitudes and NCV of nn. surales and tibiales	NRS
Week 15	Change of medication	HbA_1c_	Clinical examination NSS NDS	Bilateral amplitudes and NCV of nn. surales and tibiales	NRS Adverse events
Weekly (treatment 1–10)	Change of medication				NRS Adverse events

^a^HbA1c= glycated hemoglobin; ^b^NCV = nerve conduction velocity; ^c^NDS = neuropathy deficit score; ^d^NRS = numeric rating scale; ^e^NSS = neuropathy symptom score; ^f^NCS = nerve conduction studies

## Outcome measures

### Primary endpoint

The primary endpoint is the difference of the 15-week measurement minus baseline of the sural sensory nerve action potential amplitude (sural SNAP).

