## Statistical analysis

Major hypotheses tested are:

H0:

The differences of the 15-week measurements minus baseline of sural SNAP in the two groups with classical needle acupuncture or laser acupuncture are the same or smaller as in the control group.

vs.

H1:

The differences of the 15-week measurement minus baseline of sural SNAP in the groups with classical needle acupuncture or laser acupuncture are larger than in the control group.

In addition, for the two types of acupuncture treatment, two-sided hypotheses will be tested.

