### Data analysis

Hypotheses will be tested by using one-way analysis of variance (ANOVA), followed by Tukey post-hoc tests comparing the three groups pairwise.

A reasonable approximation to a normal distribution, according to the central limit theorem, can be assumed with the calculated sample size, allowing the use of parametric analysis. Deviations of the normal distribution will be tested and appropriate transformations will be performed. Homogeneity of variance will be tested with the Levene’s test.

The primary analysis will be performed with the intent-to-treat (ITT) population. Missing data will be imputed by the next-observation-carried-backwards option for initial values and last-observation-carried-forwards option for closing values. Legs with missing initial and closing data for the primary endpoint will be deleted from the analysis. The average values of both legs will be evaluated for patients with bilateral assessable measurements. For unilateral results, only the evaluable leg will be included in the analysis. The comparison between verum needle acupuncture and placebo laser acupuncture will be undertaken for validating the overall treatment effect of acupuncture. Verum laser acupuncture and placebo laser acupuncture will be compared for validating the specific treatment effect. The comparison of needle acupuncture to verum laser acupuncture will indicate the non-specific effect of needle acupuncture. Remaining NCS outcomes will be analyzed as described for the primary outcome. Multivariate analyses of the clinical secondary outcomes (NDS, NSS, and NRS) and their correlation to NCS parameters will be performed by linear regression models.

Baseline data and clinical characteristics will be presented as mean values to assess the baseline comparability of the intervention groups. Those patients who report changes of pain medication during the study will be excluded from data analysis relating to subjective pain scales. Statistical analysis will be done with the software SPSS (IBM SPSS Statistics 22) and OriginPro 9.

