### Sample size calculation

An average difference of 1 μV was considered functionally relevant for sural SNAP [54]. On the basis of a pilot study [24], a pooled standard deviation of 1.83 μV was calculated. By assuming that this standard deviation represents the best estimate of the actual standard deviation for each of the three groups in a regular three-arm parallel RCT design with complete follow-up, 54 patients per arm are required to detect the above difference for sural SNAP with an alpha of 0.05 and a power of 0.8. The assumption of a conservative 10% drop-out rate for patients randomized to any of the three arms increases the sample size to 60 patient per arm or 180 patients in total.

Power evaluations were performed with statistical analysis system (SAS) 9.2 for the above described statistical analysis (one-way ANOVA) and followed by post-hoc testing for the primary outcome.

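### The primary ANOVA of change in sural SNAP uses the measured baseline only by subtraction; adding it as a covariate would gain precision and protect against chance imbalance

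*Protocol article*

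**What the plan says.** The Primary endpoint section of the protocol article reads: "The primary endpoint is the difference of the 15-week measurement minus baseline of the sural sensory nerve action potential amplitude (sural SNAP". The main hypotheses in Statistical analysis concern the same differences. The model is fixed under Data analysis: "Hypotheses will be tested by using one-way analysis of variance (ANOVA), followed by Tukey post-hoc tests comparing the three groups pairwise". The Sample size calculation confirms it, because power was evaluated "for the above described statistical analysis (one-way ANOVA) and followed by post-hoc testing for the primary outcome". No covariate is named in any of these places.

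The method also covers sural SNCV, tibial MNAP and tibial MNCV: "Remaining NCS outcomes will be analyzed as described for the primary outcome". Linear regression is planned only for NDS, NSS and NRS and their correlation with the nerve conduction parameters, and its covariates are not listed.

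Table 1 schedules bilateral sural and tibial measurements at week 0. The stated role of baseline data in Data analysis is a table of means to judge comparability. The Randomization procedure is a 1:1:1 envelope lottery with no stratification described. A missing initial value is replaced by the next observation, and the next nerve conduction study after baseline is at week 6.

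**The concern.** An ANOVA of week 15 minus baseline assumes that each extra 1 μV at baseline predicts exactly 1 μV more at week 15. For a noisy measurement the slope is usually below 1, so patients with a low baseline tend to gain and those with a high baseline tend to lose, whatever their treatment. Two things follow.

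- **Precision.** The part of the change that baseline could predict stays in the error term.
- **Chance imbalance.** If one arm happens to start lower, part of its apparent gain is regression to the mean. The comparability table may show this, but the planned test does nothing about it, and no stratification is described that would limit it.

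This is not a detail left to a fuller document. The article states the primary model and bases its power evaluation on it.

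**Working it through.** **Inputs.** From the Sample size calculation: difference 1 μV, SD 1.83 μV, 54 evaluable per arm, 10% drop-out, "with an alpha of 0.05 and a power of 0.8". Not in the article, so assumed: the baseline to week-15 correlation r, the SDs s0 (baseline) and s1 (week 15), and that 1.83 μV is the SD of change.

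**1. The plan's own figure.** A two-sided 0.05 comparison of two means gives n = 53 per arm by the normal approximation and 54 with the noncentral t. Power at 54 is 0.803 with two-group error df and 0.806 with the three-group df of 159. Then 54 / 0.9 = 60 per arm, 180 in total. The stated numbers reproduce and do not depend on the present point.

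**2. Power of the planned Tukey comparison.** The standard error of a pairwise difference is 1.83 × √(2/54) = 0.352, so the noncentrality is 1 / 0.352 = 2.84. The Tukey critical value for three groups and 159 df, on the t scale, is 2.366. Power is about 0.68. This is the unadjusted reference for step 4.

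**3. Variance saved by the covariate.**
- Variance of change: s0² + s1² − 2·r·s0·s1
- ANCOVA residual variance: s1²(1 − r²)
- Difference between them: (s0 − r·s1)²

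The saving is never negative. It is zero only when s0/s1 = r, which is when the slope r·s1/s0 equals 1. With s0 = s1, the ratio of ANCOVA to change-score variance is (1 + r)/2.

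**4. Equal SDs, 54 per arm, 158 df.**

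| r | variance | residual SD (μV) | Tukey power | two-sided 0.05 power, no Tukey |
|---|---|---|---|---|
| unadjusted | – | 1.83 | 0.68 | 0.806 |
| 0.5 | −25% | 1.58 | 0.82 | 0.903 |
| 0.7 | −15% | 1.69 | 0.76 | 0.865 |
| 0.8 | −10% | 1.74 | 0.73 | 0.845 |
| 0.9 | −5% | 1.78 | 0.71 | 0.825 |

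**5. Baseline SD below week-15 SD.** The Inclusion criteria list a sural SNAP below 10 μV among the pathologic results, which could narrow the baseline distribution. Holding the SD of change at 1.83 μV:

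| r | s0/s1 | variance | Tukey power |
|---|---|---|---|
| 0.5 | 0.9 | −18% | 0.78 |
| 0.5 | 0.8 | −11% | 0.74 |
| 0.5 | 0.7 | −5% | 0.71 |
| 0.7 | 0.8 | −2% | 0.69 |
| 0.7 | 0.7 | 0% | 0.68 |

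**6. Chance imbalance, equal SDs.** The raw SD implied by 1.83 μV is s = 1.83 / √(2(1 − r)). The standard error of the baseline difference between two arms is s·√(2/54). Given an imbalance D, the expected change contrast shifts by (1 − r)·D in the opposite direction.
- r = 0.5: s = 1.83, standard error 0.352. An imbalance of 1 standard error shifts the contrast by 0.18 μV, and one of 2 standard errors by 0.35 μV.
- The 2-standard-error shift is 0.27 μV at r = 0.7, 0.22 at 0.8 and 0.16 at 0.9.

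A 2-standard-error imbalance thus moves the contrast by 16% to 35% of the 1 μV target.

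**7. If 1.83 μV is the SD of the raw amplitude instead.** With equal SDs and no Tukey adjustment, power at 54 per arm goes from 0.665 to 0.841 (r = 0.3), from 0.806 to 0.903 (r = 0.5) or from 0.954 to 0.977 (r = 0.7). The direction is the same; the size differs.

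**The case against.** The strongest reply is that nothing here is invalid. Arms are randomised, regression to the mean acts alike in all three, and the change-score test is unbiased on average and keeps its type I error. All of that stands. A reader might infer that the planned test is biased, or that selecting patients on low amplitude creates a false treatment effect. The article does not support that: the bias is conditional on a chance imbalance and averages to zero over randomisations.

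The size is also open to challenge. Neither r nor the SD ratio is given, and the article does not say which SD 1.83 μV is. If entry thresholds narrow the baseline SD while the slope stays at or below 1, the equal-SD gains are upper bounds. Averaging two legs tends to raise r, which shrinks the gain. These limits stand. A reader might also take ANCOVA as the cure for the Tukey shortfall. Among the cases shown, it restores 0.80 Tukey power only at r = 0.5 with equal SDs. The shortfall itself is a separate sample-size matter.

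Two further objections stand. For NDS, NSS and NRS the article plans regression without listing covariates, so it cannot be said that baseline is left out. And the change is not free of pitfalls: under the article's imputation rule, a missing baseline would be filled with a value measured after treatment began, which treatment may have affected and which should not serve as a covariate.

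What the reply does not remove is that the stated model leaves out a prognostic value already collected, when including it can only lower the large-sample residual variance or leave it unchanged.

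**Conclusion.** The point holds as a loss of precision and of protection against chance imbalance, not of validity. It applies to the primary endpoint and the three remaining nerve conduction outcomes. The direction does not depend on the assumptions, but the size does. Over the cases shown for 1.83 μV as the SD of change, the gain in Tukey power at 54 per arm runs from none to about 14 points (0.68 to 0.82). The upper end needs r = 0.5 and equal SDs; at r = 0.9 with equal SDs it is about 3 points. The stated 54 and 60 per arm are not wrong on this account. For NDS, NSS and NRS, baseline adjustment is a recommendation, not a demonstrated defect. The change should be made, because it improves a fully stated primary model without new data.

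**What to change.** Keep week 15 minus baseline as the endpoint. Under Data analysis, replace the one-way ANOVA with an ANCOVA:
- treatment arm as factor;
- the patient's baseline sural SNAP as covariate, averaged over the same leg or legs as the outcome;
- Tukey-adjusted pairwise contrasts taken from this model.

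Do the same for sural SNCV, tibial MNAP and tibial MNCV, each with its own baseline.

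Use only observed pre-treatment values as the covariate. Where one is missing, do not carry the next observation back into the covariate; use a fill that does not depend on treatment, such as the overall baseline mean.

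For NDS, NSS and NRS, state that the baseline score is included in the planned regression models.

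The cost is one model term, one error degree of freedom and a sentence on missing baselines, with no extra visits or patients. Because the article keeps group assignment masked until the analysis is complete, the change can be fixed in writing before unblinding.

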### Key secondary endpoints

Secondary endpoints are the differences of the 15-week measurement minus baseline of the remaining NCS measurements:

the sural sensory nerve conduction velocity (sural SNCV),

tibial motor nerve action potential amplitude (tibial MNAP),

tibial motor nerve conduction velocity (tibial MNCV).

Additional secondary endpoints will be obtained from the questionnaires:

The differences in the 15-week measurement minus baseline of NDS, NSS, and NRS scores.

## Statistical analysis

Major hypotheses tested are:

H0:

The differences of the 15-week measurements minus baseline of sural SNAP in the two groups with classical needle acupuncture or laser acupuncture are the same or smaller as in the control group.

vs.

H1:

The differences of the 15-week measurement minus baseline of sural SNAP in the groups with classical needle acupuncture or laser acupuncture are larger than in the control group.

In addition, for the two types of acupuncture treatment, two-sided hypotheses will be tested.

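### Hypotheses against control are one-sided but the planned ANOVA plus Tukey is not, and at 54 per arm it gives about 67–68% power per 1 μV contrast, not 80%

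*Protocol article*

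**What the plan says.** All of this is in the protocol article.

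- **Statistical analysis.** Under the null, changes in the needle and laser groups "are the same or smaller as in the control group"; under the alternative they "are larger than in the control group". Both active arms appear in a single pair of statements. The section then adds: "In addition, for the two types of acupuncture treatment, two-sided hypotheses will be tested".
- **Data analysis.** The procedure is fixed as follows: "Hypotheses will be tested by using one-way analysis of variance (ANOVA), followed by Tukey post-hoc tests comparing the three groups pairwise". Each of the three pairs has a stated purpose, including the active-versus-active one: "The comparison of needle acupuncture to verum laser acupuncture will indicate the non-specific effect of needle acupuncture".
- **Sample size calculation.** "An average difference of 1 μV was considered functionally relevant for sural SNAP". With a pooled SD of 1.83 μV, 54 patients per arm are said to suffice "with an alpha of 0.05 and a power of 0.8", rising to 60 per arm for 10% drop-out. Sidedness is not given. The section says power was evaluated for the one-way ANOVA and the post-hoc tests after it.

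**The concern.** The hypotheses separate one-sided contrasts against control from a two-sided contrast between the two active treatments. The analysis drops that separation. The F-test asks only whether three means differ, and Tukey is two-sided over all pairs, so no directional test is named for a directional hypothesis.

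The sample size is tied to a third thing. It is presented as the power of the ANOVA with post-hoc testing, yet it looks like the size for one unadjusted two-group comparison. If so, the trial is less likely to detect its own relevant difference in either active arm than stated, and a null result would be read as coming from an 80%-powered comparison.

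**Working it through.** **Inputs (Sample size calculation):** difference 1 μV, SD 1.83 μV, alpha 0.05, power 0.80, 54 evaluable per arm, three arms. Residual df = 3 × 54 − 3 = 159.

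**1. Reproduce 54.** Normal approximation, two-sided: n = 2 × (1.960 + 0.842)² × 1.83² / 1² = 52.6, so 53. The noncentral-t version of the same unadjusted two-group test gives exactly 54 (power 80.3%, or 80.6% with 159 df). Then 54 / 0.90 = 60, as stated.

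**2. Other tests, n per arm for 80% power:**

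| Test | n per arm |
|---|---|
| One-sided t-test, unadjusted | 43 |
| Overall F-test, means (0,1,1) or (0,0,1) | 50 |
| Overall F-test, means (0,0.5,1) | 66 |
| One-sided 5% Dunnett | 52 |
| Two-sided 5% Dunnett | 64 |
| Tukey, one pair | 69 |

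Means are listed as placebo first, then the two active arms. None of these gives 54.

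**3. Power of the planned pairwise test at 54.** SE of a pairwise difference = 1.83 × √(2/54) = 0.352 μV. Tukey's critical t at 159 df is 2.366, so the observed difference must exceed 2.366 × 0.352 = 0.83 μV. The unadjusted two-sided test needs 1.975 × 0.352 = 0.70 μV. Approximate Tukey power = Φ(1/0.352 − 2.366) = Φ(0.47) = 0.68; the noncentral-t value is 68.2%.

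**4. Gated procedures, by simulation (300,000 trials, n = 54), for a true 1 μV contrast with placebo:**

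| True means | F-test rejects | F, then Tukey | F, then unadjusted t |
|---|---|---|---|
| (0,1,1) | 83.7% | 67.9% | 76.4% |
| (0,0,1) | 83.8% | 67.9% | 76.4% |
| (0,0.5,1) | 71.2% | 66.8% | 70.0% |

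If all 60 per arm were evaluable, F then Tukey would give 72–73% and F then unadjusted t 75–81%.

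**5. Error rates.** Under the global null, at least one active arm is falsely shown superior in about 1.8% of trials with Tukey (1.6% with the F gate). The F-test alone does not address the stated alternative: with both active arms 1 μV worse than placebo it still rejects in 83.7% of trials.

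**6. Why unadjusted tests suffice after the F gate.** With three means, if any two pairwise nulls are true then all three means are equal. The only intersection to protect is therefore the global null, which the F-test covers at 0.05. If exactly one pairwise null is true, it is tested once at 0.05. Simulated family-wise error is 4.97% under the global null and 4.9% for the one true null under (0,0,1).

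**The case against.** Much of the case for the plan stands.

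- **Validity.** A two-sided test of a directional hypothesis does not inflate type I error. The only cost is power.
- **All-pairs testing has a purpose.** Needle versus verum laser is a planned two-sided comparison, and Tukey is a standard method for three planned pairs. It is excess only in the sense that a more powerful procedure covers the same three pairs at the same family-wise level.
- **Three success thresholds.** A reader might infer that the three sections set three competing cut-offs, so that the same data could pass or fail. The document does not support this. The hypotheses carry no critical value, the sample size section sets no decision rule, and only Data analysis names a test.
- **Paying for multiplicity twice.** This is also tempting, but the F gate costs only about 0.4 to 1.4 percentage points beyond Tukey alone. Tukey's critical value causes most of the loss. Nor does the text say outright that the F-test is a gate.
- **Power for at least one arm.** If both active arms truly gain 1 μV and either would suffice, F plus Tukey finds at least one superior in 82% of trials. On that reading 80% is met. But the text states no such rule, 54 reproduces as a single-contrast calculation, and if only one arm works the figure falls back to 68%.
- **A fuller plan may exist.** Gating and either/both rules may be set there, so their absence here is not the point. The point is that the hypotheses, test and power that are stated do not match.

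**Conclusion.** The mismatch is real but moderate. One-sided hypotheses are tested by a non-directional F-test and two-sided Tukey. That is safe for false positives: about 1.8% for any false superiority claim, below a one-sided 5% and also below 2.5%. The stated 80% power belongs to an unadjusted two-sided t-test. The planned F-test plus Tukey delivers about 67–68% per 1 μV contrast at 54 evaluable per arm, a shortfall of 12 to 13 points.

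These figures rest on the plan's own SD and difference, normal errors with equal variances, and the F-test acting as a gate. Without the gate, Tukey gives 68.2%. They concern one contrast with placebo. Power to win on both arms would be lower, but the document does not require both.

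**What to change.** 1. State sidedness and alpha once. Write separate hypotheses for needle versus placebo and verum laser versus placebo, each two-sided at 0.05, with benefit claimed only if the estimate favours the active arm. Keep needle versus verum laser as the additional two-sided comparison.
2. Since an F-test already precedes the pairwise tests and there are exactly three groups, make it an explicit gate at 0.05. If it is significant, use unadjusted two-sided pairwise t-tests from the same model. This rejects whenever F plus Tukey does, and more often, at 5% family-wise error.
3. Replace the 80% with the power of the procedure kept, at 54 evaluable per arm: about 67–68% per contrast for F plus Tukey, or 70–76% for the closed test, depending on the third mean.

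The cost is wording in the analysis and sample size sections, settled before unblinding, with no more patients enrolled. One downside: Tukey simultaneous intervals would no longer correspond to the test decisions. The closed test also stays below 80% at 54 per arm, so it narrows the gap without closing it.
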